#### In participants resistant to fluoroquinolones

Pre-XDR TB participants are identified with the Xpert MTB/XDR assay prior to treatment initiation. The experimental arm is a 9-month regimen consisting of bedaquiline, cycloserine, clofazimine, linezolid and pyrazinamide. Treatment could be extended to 11 months if cavities are present at month 9 or in case of a positive culture at month 2. Pyrazinamide will be discontinued from the study regimen if baseline WGS results reveal pyrazinamide resistance.

The comparator is a conventional longer regimen consistent with the national guidelines [11], including bedaquiline, cycloserine, clofazimine and linezolid. Treatment duration is 20 months, with a 6-month intensive phase and a 14-month continuation phase. Composition of the study regimen and dosing is described respectively in Tables 1 and 2.

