#### Follow-up duration and participant timeline

The baseline visit includes collection of medical history, a physical examination, evaluation of symptoms and signs, laboratory tests, a 12-lead electrocardiogram, visual acuity assessment, assessment for peripheral neuropathy, smear, culture, and the Xpert MTB/XDR assay. During the treatment period, follow-up visits are scheduled monthly until treatment completion. After treatment, visits are conducted every three months in the first six months, and then every six months until 21 months after randomisation. Additional visits could be conducted as clinically needed. Follow-up assessment during treatment and post-treatment assessment are shown in Table 3. MTB strains are collected and sent to the central lab for whole genome sequencing at baseline and post-baseline visits as needed.

**Table 3 Tab3:** Schedule of enrolment, interventions, and assessments

	Baseline	Treatment Period						Post-treatment Period		
		monthly						M12	M15	EOS^#^
Timepoint (month)	-2 weeks to M0	M1	M2	M3		…	EOT^**^			
Inform consent	**×**									
Eligibility assessment	**×** ^*****^									
Treatment allocation	**×**									
Susceptibility testing for rifampicin	**×**									
Rapid molecular test for FQ resistance	**×**									
Treatment adherence assessment		**×**	**×**	**×**		**×**	**×**			
Evaluation of signs and symptoms	**×**	**×**	**×**	**×**		**×**	**×**	**×**		**×**
Sputum Tests (smear and culture)	**×**	**×**	**×**	**×**		**×**	**×**	**×**		**×**
Electrocardiogram	**×**	**×**	**×**	**×**		**×**	**×**	if indicated		
Routine blood tests and chemistry	**×**	**×**	**×**	**×**		**×**	**×**	if indicated		
Chest Radiography	**×**	if indicated			**×**			if indicated		
Haemoglobin A1c	**×**	Every three months in participants with diabetes								
TSH, FT3, FT4	**×**	monthly if on prothionamide								
HIV test, hepatitis B and C	**×**									
Pregnancy test	**×**									
Visual acuity assessment	**×**	if indicated						if indicated		
Assessment for peripheral neuropathy	**×**	if indicated						if indicated		
SDS and SAS	**×**	if indicated						if indicated		

Abbreviation: EOT: end of treatment; EOS: end of study; TSH: thyroid-stimulating hormone; FT3: free triiodothyronine; FT4: free thyroxine; SDS: self-rating depression scale; SAS: self-rating anxiety scale

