^*^ Sputum rapid molecular test for rifampicin resistance should be performed during screening for eligibility assessment, and rapid molecular test for fluoroquinolone resistance should be acquired before randomisation for stratification

^**^ Timepoint of EOT in Regimen A1, A2, A3, A4, A5 and B1 is 9 months. Timepoint of EOT in Regimen B-SOC is 20 months

^#^ Timepoint of EOS is 21 months after randomisation

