^b^ Loss to follow-up is defined in case that a participant fails to complete two or more consecutive scheduled visits and cannot be reached after at least three phone calls and one home interview

Main secondary outcomes are measured in fluoroquinolone-susceptible and fluoroquinolone-resistant arms respectively. Secondary outcomes are defined as follows:

Time to sputum smear conversion in the mITT population.Time to sputum culture conversion in the mITT population.The proportion of participants with a favourable outcome at 21 months post-randomisation in the per-protocol (PP) population.The proportion of participants with grade 3 or higher adverse event (AEs), serious adverse events (SAEs) at 21 months post-randomisation in the safety population.All-cause mortality and treatment relevant mortality at 21 months post-randomisation in the safety population.The proportion of participants with treatment relevant SAEs at 21 months post-randomisation in the safety population.The proportion of participants with grade 3 or higher QTc prolongation in the safety population.The proportion of participants experiencing permanent drug discontinuation or replacement due to QTc prolongation in the safety population.

Exploratory outcome measures are defined as the following:

The proportion of participants with a favourable outcome at 21 months after randomisation in regimen A2a, A2b and A2c in the mITT population.The proportion of participants with grade 3 or higher myelosuppression, peripheral neuropathy and optic neuropathy in regimen A2a, A2b and A2c in the safety population.The proportion of participants with linezolid discontinuation or dose reduction due to AE in regimen A2a, A2b and A2c in the safety population.

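### Group B: scheduled ECG and blood tests run to month 20 in B-SOC but to month 9 in B1, so a crude 21-month grade 3+ proportion mixes toxicity with testing intensity

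*Protocol article*

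**What the plan says.** Four statements in the protocol article combine here.

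- **Visits.** Follow-up duration and participant timeline: "During the treatment period, follow-up visits are scheduled monthly until treatment completion". After that, "After treatment, visits are conducted every three months in the first six months, and then every six months until 21 months after randomisation".
- **Tests.** In Table 3 the ECG row and the row "Routine blood tests and chemistry" are marked at baseline and at each treatment visit up to end of treatment. In the post-treatment columns both are done only on indication. Signs and symptoms and sputum tests remain scheduled after treatment.
- **End of treatment.** Table 3 footnotes: "Timepoint of EOT in Regimen A1, A2, A3, A4, A5 and B1 is 9 months", whereas "Timepoint of EOT in Regimen B-SOC is 20 months". End of study is month 21 in both arms. For B1 the regimen section adds: "Treatment could be extended to 11 months if cavities are present at month 9 or in case of a positive culture at month 2".
- **Outcome.** Outcome measurements lists "The proportion of participants with grade 3 or higher adverse event (AEs), serious adverse events (SAEs) at 21 months post-randomisation in the safety population". The grade 3+ QTc outcome is listed without a time window.

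The statistical section describes grade 3–5 AEs, SAEs and treatment-related SAEs by numbers and percentages, with no test or margin. The Safety section collects AEs from consent to the last known visit in every arm.

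**The concern.** Some grade 3+ events cause no symptoms and come to light only when blood is drawn or an ECG is recorded. From month 10 to month 20, B-SOC participants have these tests every month by schedule, while B1 participants have them only if a clinician sees a reason. The trial is open-label, so that decision is made with knowledge of the arm. AE collection nevertheless continues in B1, so the months without scheduled tests count as follow-up in the 21-month proportion.

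A lower B1 figure could then have three sources: a less toxic regimen, fewer months on drug, or fewer tests. The first two are real effects of the strategy and the third is not. The protocol sets out to compare the safety of B1 with that of the 20-month regimen, and its Discussion hopes for safer short regimens, so readers will compare these percentages even though they are descriptive.

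The point is specific to Group B, because nominal treatment duration is 9 months in every Group A arm.

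**Working it through.** The documents state no safety rate or detection figure, so there is no figure of the plan's own to reproduce. The check has two parts: a count from the schedule, and an illustration under stated assumptions.

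**1. Scheduled post-baseline ECG and blood checks to month 21**

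| | B-SOC | B1 | B1 if extended |
|---|---|---|---|
| Monthly checks on treatment | 20 | 9 | 11 |
| Months to month 21 without scheduled checks | 21 − 20 = 1 | 21 − 9 = 12 | 21 − 11 = 10 |

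The ratio of checks is 20/9 = 2.2, or 20/11 = 1.8 if extended. After month 9 the nominal B1 visits fall at about months 12, 15 and 21, with no scheduled ECG or blood test.

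**2. How much could be missed**

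Assumptions, none of them from the documents:
- h = monthly on-treatment risk of a test-detectable grade 3+ event, set to 1%.
- r = post-treatment risk as a fraction of h.
- d = share of post-treatment events found without a scheduled test.

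Formulas:
- B1 true proportion = 1 − (1 − h)^9 × (1 − rh)^12
- B1 observed proportion = 1 − (1 − h)^9 × (1 − rhd)^12
- B-SOC: the same, with exponents 20 and 1

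With h = 0.01, 0.99^9 = 0.9135 and 0.99^20 = 0.8179. The observed B-SOC proportion with d = 0 is 1 − 0.8179 = 18.2%. B-SOC's own loss in its single untested month is 0.8179 × rh(1 − d). The net column subtracts that loss from the B1 loss.

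| r | d | B1 true | B1 observed | Missed in B1 (points) | Net of B-SOC (points) |
|---|---|---|---|---|---|
| 0 | any | 8.65% | 8.65% | 0 | 0 |
| 0.25 | 0.5 | 11.35% | 10.01% | 1.3 | 1.34 − 0.10 = 1.2 |
| 0.25 | 0 | 11.35% | 8.65% | 2.7 | 2.70 − 0.20 = 2.5 |
| 0.5 | 0.5 | 13.98% | 11.35% | 2.6 | 2.63 − 0.20 = 2.4 |
| 0.5 | 0 | 13.98% | 8.65% | 5.3 | 5.33 − 0.41 = 4.9 |
| 1 | 0.5 | 19.03% | 13.98% | 5.0 | 5.05 − 0.41 = 4.6 |
| 1 | 0 | 19.03% | 8.65% | 10.4 | 10.38 − 0.82 = 9.6 |

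In the last two rows both arms have the same true risk throughout, so the net figure is the whole observed difference (18.2% against 8.65% with d = 0). If every B1 participant were extended to 11 months, those two net figures would be 3.8 and 7.7 points. With d = 1, all differences due to detection vanish.

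For scale, at the planned 117 per arm, 1.3 to 2.7 points is about 2 to 3 B1 participants (117 × 0.0134 = 1.6; 117 × 0.027 = 3.2).

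**The case against.** A reader might infer more than the schedule supports. If each check carries the same chance of a finding, the proportion with at least one is 1 − (1 − p)^n. With n = 9 against n = 20 this gives 2.2% against 4.9% (p = 0.25%), 4.4% against 9.5% (p = 0.5%) and 8.6% against 18.2% (p = 1%). It is tempting to call these 3 to 10 points an effect of detection and observation time alone. The documents do not support that. The whole gap arises in months 10–20, when B-SOC participants are still taking linezolid, cycloserine and clofazimine (Table 1) and B1 participants have stopped. Events caused by those extra months are real harm of the longer regimen. The gap is purely detection only if people off treatment carry the same risk as people on it.

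Four further objections carry weight:
- A fixed 21-month window from randomisation is a sound comparison of whole strategies, since fewer months of exposure is part of what the short regimen offers. This stands, and the 21-month figure should stay.
- Symptoms are reviewed at post-treatment visits, tests on indication remain possible, and AEs are collected to the last visit. Deaths and clinically presenting SAEs therefore depend little on the schedule. This stands and limits the point to silent, test-detected events.
- For QTc, a constant risk over 20 months does not match the regimens: Table 1 gives bedaquiline for 6 months in B-SOC and lists it for the 9-month course in B1. A months 0–9 window therefore equalises testing but not drug composition. This stands as a limit on interpretation. It also means the extra B-SOC ECGs could mask a B1 excess as well as create an apparent advantage.
- The article is condensed and the analysis plan is not shown, so one cannot conclude that no windowed analysis exists. This stands too. The point concerns how the stated schedule, window and summary combine, and that combination is in the article.

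**Conclusion.** The point holds as a caution about ascertainment, with a cheap remedy. The unequal schedule is plain in the article, and its direction after month 9 is clear: silent laboratory- or ECG-detected grade 3+ events are less likely to be found in B1 than in B-SOC. The stated 21-month proportion cannot separate that from the true effect of longer treatment, and the QTc outcome has no stated window.

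The size cannot be derived from the documents. Everything depends on the post-treatment risk in B1 and on how often unscheduled testing finds events. Under the assumed 1% monthly risk, the range runs from nothing to about 9.6 points. The upper end needs undiminished risk after stopping treatment and no unscheduled detection at all. The documents do not show that B1 will look safer by any particular amount for this reason, nor that a B1 advantage would be spurious.

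**What to change.** Change the analysis and leave the treatment schedule as it is. Before database lock:

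1. Keep the 21-month proportions as the comparison of whole strategies.
2. Pre-specify for Group B a comparison of grade 3+ AEs and of grade 3+ QTc prolongation over months 0–9, when both arms have the same monthly schedule, and state the window of the QTc outcome.
3. Split the 21-month grade 3+ events into those found by test and those presenting clinically. The AE fields listed in the Safety section do not include mode of detection, so fix the rule in advance, for example by AE term or by linkage to test dates.
4. State beside the 21-month figures that testing after month 9 (month 11 for extended B1 participants) was scheduled in B-SOC and on indication in B1.

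If the full protocol or analysis plan already contains such a comparison, a cross-reference is enough.

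The cost is one extra table from data already collected. The apparent safety advantage of B1 may be smaller in the common window, and months 0–9 alone do not capture the burden of longer treatment, which is why both presentations are needed. Group B enrolment is complete, so equalising the tests themselves would help only participants still in follow-up.

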#### Randomisation

Randomisation is based on an online system (REDCap) operated remotely at Huashan Hospital, Fudan University and is stratified by research sites. Prior to randomisation, patient eligibility is re-confirmed through a comprehensive review of medical history. An individualized eligibility assessment was documented in the electronic case report form, capturing detailed data on drug susceptibility, contraindications, concomitant medications, and treatment tolerance, as specified in the Supplementary Materials. Patients with known resistance or contraindications to regimen components are excluded from the randomisation procedure and receive guideline-based standard care. Eligible participants will be stratified into fluroquinolone-susceptible arms (group A) and fluoroquinolone-resistant arms (group B) based on baseline Xpert MTB/XDR results.

In group A, the randomisation ratio between the regimen A-SOC and each experimental arm is 1:1. Enrolment into the experimental arm will be ceased once its planned sample size is reached. Participants resistant to fluoroquinolones are randomised to regimen B1 and regimen B-SOC in a 1:1 ratio.

In response to updated RR-TB treatment guidelines and emerging evidence, this trial was strategically optimized in 2024. The initial design included a bedaquiline-free arm (regimen A5). Following WHO’s endorsement of bedaquiline-based oral shorter regimens [13, 14], the study protocol was amended in version 6.0 (November 2024) to discontinue the enrolment of regimen A5, ensuring sufficient sample size for evaluation of bedaquiline-containing arms. In addition, randomisations to regimen A2b and A2c were halted based on two primary considerations. First, a recently published multicentre randomised controlled trial demonstrated the non-inferior efficacy of a nearly identical structured linezolid dose-reduction strategy [15], thereby compromising the novelty of our pre-planned analysis. Second, enrolment has progressed more slowly than we initially anticipated. Therefore, a strategic decision was made to concentrate limited resources to prioritize the remaining arms to address critical evidence gaps in RR-TB treatment.

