#### Sample size assumptions

The sample size calculation was performed in PASS 11 system (NCSS, Version 11.0.10). In an individual patient data meta-analysis of 13,273 MDR/RR-TB patients from 38 countries, the treatment success rate of the bedaquiline-containing oral shorter regimen is 73% [16]. We thus assume a 70% favourable rate in the control arm and 80% in the experimental arms in fluoroquinolone susceptible patients. Since multiple experimental groups are simultaneously compared with the control group, the family-wise type I error will be controlled by a fixed sequence approach. The experimental groups are tested sequentially in a pre-specified order, and if any group fails to demonstrate non-inferiority, testing for subsequent groups will be discontinued. All the previous comparisons will be done at the one-sided alpha level of 2.5%. Therefore, a sample size of 73 per arm will afford 80% power to establish non-inferiority of seven experimental regimens with a non-inferiority margin of 10% at a one-sided α level of 2.5%. The number excluded from the modified intention-to-treat population is estimated to be 30% and therefore the recruitment target is increased to 104 per arm. The total sample size of fluoroquinolone-susceptible RR-TB participants is 832.

By November 2024, randomisation to regimen A2b, A2c as well as A5 has been ceased following protocol amendment. The actual number of enrolled participants at the time of early closure were 73, 72, 92 respectively in regimen A2b, A2c and A5. Therefore, the total sample size of fluoroquinolone-susceptible RR-TB participants have been adjusted to 520 (including regimen A1, A2a, A3, A4 and A-SOC).

In fluoroquinolone-resistant RR-TB participants, we assume that 75% of participants in the experimental arm (regimen B1) and 65% of participants in the control arm (regimen B-SOC) will achieve a favourable outcome. A sample size of 82 per arm will afford 80% power to establish non-inferiority with a margin of 10% and a one-sided α level of 0.025. The number excluded from the modified intention-to-treat population is estimated to be 30% and therefore the recruitment target is increased to 117 per arm. The total sample size of fluoroquinolone-resistant participants is 234.

As of September 2025, enrolment for the fluoroquinolone-resistant group has completed, while recruitment of fluoroquinolone-susceptible participants remains ongoing.

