Similar to the endTB trial, this study adopts a pragmatic approach to evaluate candidate regimens in real world clinical settings. First, the INSPIRE TB study applies minimal inclusion and exclusion criteria, enrolling a broad spectrum of patients with varying disease severity, comorbidities and HIV status. Second, this trial is conducted across multiple clinics and hospitals nationwide by staff engaged in routine clinical care, thereby simulating real-world conditions. Third, the study protocol allows appropriate drug modifications in response to safety events or treatment failure, aligning with standard RR-TB management. As the WHO has called for evaluation of newly-recommended regimens across different regions and populations [13, 20], our study aims to contribute critical evidence to address this gap.

The INSPIRE TB trial initially incorporated regimen A2a, A2b and A2c to investigate a structured linezolid dose-reduction strategy in RR-TB treatment. Currently, there remains no consensus on the optimal dosing and treatment duration of linezolid, with strategies varying widely across trials. The ZeNix trial previously evaluated four linezolid doses (1200 mg daily for 26 weeks, 1200 mg daily for 9 weeks, 600 mg daily for 26 weeks, and 600 mg daily for 9 weeks), with safety and efficacy outcomes favouring the 600 mg/day 26-week regimen [21]. In the TB‑PRACTECAL trial, linezolid was administered at 600 mg per day for 16 weeks, followed by 300 mg per day for 8 weeks [22]. Our initial design planned to assess three linezolid dosing group: 600 mg daily for 9 months, 600 mg daily for 2 months, 600 mg daily for 2 months followed by 300 mg daily. However, during the trial enrolment phase, emerging evidence from clinical trials adopting similar strategy has prompted a re-evaluation of study design [15]. Concurrently, trial recruitment has been slower than we anticipated, which necessitated the discontinuation of randomisation to regimens A2b and A2c to ensure adequate sample size for the remaining arms. Despite this, safety and efficacy data from regimen A2b, A2c will be reported as exploratory analyses to provide knowledge for optimal linezolid dosing within a 9-month bedaquiline-based oral regimen for fluoroquinolone-susceptible RR-TB.

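### The exploratory linezolid outcomes set A2a, still recruiting, beside A2b and A2c, closed by November 2024, with no limit to concurrent patients; closed arm A5 is named in no efficacy outcome

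*Protocol article*

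**What the plan says.** All references are to the protocol article.

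- **Closure.** Under Sample size assumptions, randomisation to A2b, A2c and A5 had ended by November 2024: "The actual number of enrolled participants at the time of early closure were 73, 72, 92 respectively in regimen A2b, A2c and A5". The group A total was reset to 520, counting A1, A2a, A3, A4 and A-SOC.
- **Continuing arms.** Table 1 lists A-SOC, A1, A2a, A3 and A4 as recruiting. Group A recruitment was still open in September 2025. The Randomisation section adds: "Enrolment into the experimental arm will be ceased once its planned sample size is reached".
- **Exploratory outcomes.** Under Outcome measurements, the efficacy item is "The proportion of participants with a favourable outcome at 21 months after randomisation in regimen A2a, A2b and A2c in the mITT population". Two safety items name the same three regimens in the safety population.
- **Populations.** The mITT population is defined by culture, susceptibility results, randomisation in error and receipt of treatment. Calendar period plays no part. ITT covers everyone randomised, and the safety population everyone dosed.
- **Fate of the closed arms.** The Discussion states that "safety and efficacy data from regimen A2b, A2c will be reported as exploratory analyses", to add to knowledge on linezolid dosing. It makes no such statement for A5.

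**The concern.** A2a, A2b and A2c share the same drugs and differ in linezolid dose or duration, so the contrast between them is the reason for listing them together. That contrast is randomised only among patients who could have been allocated to any of the three. A2a patients randomised after the closure could not. If case mix, care or outcome ascertainment moved over calendar time, the movement enters the A2a rate and not the A2b or A2c rates, and it would look like a linezolid effect. The article itself describes guideline changes and new evidence in 2024, so some movement is plausible, though no size is given.

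The second issue is A5, the only bedaquiline-free experimental arm and the largest of the three that closed (92 of a planned 104, or 88%). A2b and A2c are given a named exploratory efficacy outcome and A5 is not. The article also does not say whether the closed arms have left the fixed sequence. Under that procedure the first failure ends testing, so an undersized closed arm placed ahead of a continuing arm could block it.

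**Working it through.** **1. The plan's own figures.** The planning assumptions are: "We thus assume a 70% favourable rate in the control arm and 80% in the experimental arms in fluoroquinolone susceptible patients", margin 10 points, one-sided alpha 2.5%, power 80%.

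n per arm = (1.96 + 0.842)² × (0.8×0.2 + 0.7×0.3) / (0.10 + 0.10)² = 7.85 × 0.37 / 0.04 = 72.6, so 73. This agrees with "a sample size of 73 per arm will afford 80% power to establish non-inferiority of seven experimental regimens". Then 73 / 0.70 = 104.3 (stated 104), 104 × 8 = 832 and 104 × 5 = 520. The sample-size figures are sound, and the point does not rest on an error in them.

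**2. Non-concurrent share of A2a.** The article does not give A2a enrolment at closure. I assume it lay in the range seen in the closed arms, 72 to 92.

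- 72 enrolled: (104 − 72) / 104 = 31%
- 73 enrolled: (104 − 73) / 104 = 30%
- 92 enrolled: (104 − 92) / 104 = 12%

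Applying the plan's 30% mITT exclusion evenly over time leaves these shares unchanged within mITT.

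**3. Bias.** Bias = non-concurrent share × drift, where drift is the difference in favourable rate between later and earlier patients. The 5 and 10 point values are assumptions.

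| A2a at closure | drift 5 points | drift 10 points |
|---|---|---|
| 72 | 1.5 | 3.1 |
| 92 | 0.6 | 1.2 |

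**4. Bias against precision.** mITT sizes are 73 for a full A2a and 73 × 0.70 = 51 for A2b. At an 80% favourable rate in both, the 95% CI half-width is 1.96 × √(0.16/73 + 0.16/51) = 14.3 points.

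**5. Cost of restricting A2a to concurrent patients.** If A2a had 73 enrolled at closure, it keeps about 51 in mITT. The half-width becomes 1.96 × √(0.16/51 + 0.16/51) = 15.5 points. The standard error ratio is √(2/51) / √(1/73 + 1/51) = 1.085, an increase of about 8%.

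**6. What A5 could still show.** 92 × 0.70 = 64 in mITT. If A-SOC had 72 to 92 enrolled at closure (assumed), it has about 50 to 64 in mITT. At 80% versus 70% the half-width is 1.96 × √(0.16/64 + 0.21/64) = 14.9 points with 64 controls, and 1.96 × √(0.16/64 + 0.21/50) = 16.0 points with 50. That is close to the precision of the linezolid comparisons the article already plans.

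**7. Does the same problem reach the primary comparisons?** It would if a continuing arm filled well before A-SOC. The only evidence of unequal filling is 73, 72 and 92. With an expected 79 each, chi-square = (36 + 49 + 169) / 79 = 3.2 on 2 degrees of freedom, p about 0.20. These counts are compatible with chance and do not support a forecast. Restricting the primary comparisons would also cost power. If, for illustration, A-SOC had 81 enrolled when an experimental arm filled, 81 × 0.70 = 57 controls would remain against 73. The standard error is √(0.16/73 + 0.21/57) = 0.0767, and 0.20/0.0767 − 1.96 = 0.65, so power falls from about 80% to about 74%.

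**The case against.** The strongest reply is that the article never says A2a will be compared in full with A2b and A2c. It lists proportions by regimen and gives no contrast, test or period. Handling of non-concurrent patients is usual material for an analysis plan, which is not shown. That is fair as far as it goes: the text does not decide to pool periods, and a fuller document may restrict them. What stands is that the article, written after the amendment, does name the regimens and the population for these outcomes. Following that text puts later A2a patients beside closed arms in order to inform linezolid dosing.

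It is also true that these outcomes are exploratory, that no confirmatory claim rests on them, and that the bias is small beside the interval. Drug choice within A-SOC cannot affect A2a versus A2b or A2c. These points limit the weight of the finding without removing it.

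On A5, a reader might infer that its 92 patients have no planned analysis or are discarded. The article does not support that. They are in the ITT and safety populations, efficacy in ITT is a supportive analysis, and the secondary outcomes for the fluoroquinolone-susceptible arms do not exclude them. The 520 is a recruitment target and does not define an analysis set. Nor is A5 the only arm that may lack bedaquiline, because Table 1 allows linezolid in its place in A-SOC. What remains is that no efficacy outcome names A5 and its place in the testing sequence is unstated.

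**Conclusion.** The point holds for the exploratory comparisons and for the status of A5. On the text as it stands, about 12% to 31% of A2a would be non-concurrent with A2b and A2c, giving a bias of about 0.6 to 3.1 points. Both figures rest on assumptions: 72 to 92 enrolled in A2a at closure, and a drift of 5 to 10 points. The bias could go in either direction. It is modest against a half-width of about 14 points, but it is avoidable with data already held.

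A reader might go further and infer that the primary non-inferiority comparisons are compromised because arms fill at different speeds, or that every comparison should be cut to concurrent patients. The documents do not establish the first, since the closed-arm counts are compatible with chance and A-SOC has the same target and a 1:1 ratio to each experimental arm. The second is a trade-off, because it could lower primary power to about 74%. This is an inexpensive improvement to the exploratory analyses and does not amount to a defect in the primary analysis.

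**What to change.** 1. State that the exploratory comparisons of A2a with A2b and A2c, for efficacy and safety, use participants randomised up to the closure date, with the all-patients analysis as sensitivity.
2. Add A5 versus concurrently randomised A-SOC, for favourable outcome and safety, to the exploratory outcomes.
3. State that A2b, A2c and A5 are outside the fixed sequence.
4. For the primary comparisons of the continuing arms, keep the analysis as planned and add a concurrent-control analysis as sensitivity only.
5. Report A2a and A-SOC enrolment at the closure date, so that the non-concurrent share is known.

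Randomisation dates should already be held, so no new data are needed. The cost is a standard error about 8% larger for A2a versus A2b if A2a drops from 73 to about 51 mITT patients, plus a little more analysis work. Primary power is unaffected.
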